#### Adverse events and abnormal laboratory results

All adverse events observed or reported by patients will be recorded in the CRF with information about severity and possible relation to the study medication. Any serious adverse effects will be notified immediately to the study monitor. The investigator will report the same to the ethics committee and ICMR at the earliest. The follow-up of abnormal laboratory tests described in the CRF will be recorded accordingly.

#### Safety recording

Safety evaluation will be performed by recording clinical adverse events at randomization (baseline) and at the subsequent clinical visits. Further adverse events will be classified according to their type, severity, and possible relationship to treatment. At visit 1, the subject’s medical history will be recorded. At all visits, the vital signs, i.e., body temperature, pulse, blood pressure, will be recorded and urine for routine microscopy will be performed. Antenatal checkup will be performed as per hospital protocol and time and mode of delivery will also be as per obstetrical indication.

### Frequency and plans for auditing trial conduct

#### Project Management Group (PMG)

Frequency of meetings: the PMG will meet every 6 months to review the trial’s overall conduct. These meetings will facilitate continuous oversight and timely resolution of any issues.

#### Agenda

The meetings will focus on key performance indicators, recruitment rates, data collection progress, protocol adherence, and emerging challenges. Deviations from the protocol will be discussed, and corrective actions will be implemented as needed.

#### Documentation

Minutes from each PMG meeting will be recorded, detailing decisions, assigned actions, and follow-up deadlines. These minutes will be distributed to all PMG members.

### Trial steering group (TSG)

#### Frequency of meetings

The TSG will convene quarterly to provide strategic oversight and review the trial’s progress. Meetings will occur every 3 months to ensure alignment with study objectives and to address high-level issues.

#### Responsibilities

The TSG will review interim results, assess trial conduct, and make recommendations for protocol adjustments if necessary. They will also address any ethical or scientific concerns that arise.

#### Documentation

Detailed records, including minutes and resolutions, will be maintained from each TSG meeting to track the trial’s progress and guide decision-making.

### Independent Data Monitoring and Ethics Committee (DMC)

#### Frequency of meetings

The DMC will meet semi-annually to review interim data and ensure the trial’s integrity and participant safety. More frequent meetings may be scheduled if required based on emerging data or specific concerns.

#### Responsibilities

The DMC will review unblinded data to monitor safety, assess efficacy, and ensure ethical conduct of the trial. Recommendations regarding trial continuation, modifications, or early termination will be made as needed.

#### Documentation

The DMC will prepare and submit detailed reports on their findings and recommendations. These reports will be shared with both the TSG and PMG to inform ongoing trial management.

### Adherence to protocol and quality assurance

#### Internal audits

Regular internal audits will be performed to evaluate compliance with the study protocol, data accuracy, and overall quality. These audits will occur at least annually and may be conducted by the research team or an independent auditor.

#### External audits

The trial may undergo external audits by regulatory bodies or funding agencies to ensure adherence to regulatory and ethical standards. These audits will follow the schedule set by regulatory guidelines and funding requirements.

#### Corrective actions

Issues identified during audits or meetings will be promptly addressed. The PMG will oversee the implementation and effectiveness of corrective actions to ensure the trial’s integrity.

### Data and Safety Monitoring Board (DSMB)

A Data and Safety Monitoring Board (DSMB) will be established specifically for this trial. The DSMB will consist of independent members with relevant expertise, such as clinical researchers, biostatisticians, and ethicists. These members will have no affiliation with the trial sponsor to ensure objectivity and avoid conflicts of interest.

### Composition and independence

The DSMB will be composed of individuals who are not involved in the day-to-day management of the trial and who have no competing interests. This ensures independent oversight, with members chosen for their expertise in the specific clinical, statistical, and ethical domains pertinent to the study. The DSMB will function autonomously from the sponsor, providing unbiased assessments and recommendations.

### Role and reporting structure

The DSMB will meet periodically to review and evaluate accumulated data, with the following primary responsibilities:

Monitor participant safety and the overall conduct of the trial.Assess the trial’s progress, including safety and efficacy data, where applicable.Make recommendations regarding the continuation, modification, or early termination of the trial based on their analysis.

The DSMB will report its findings directly to the trial sponsor and relevant regulatory authorities, maintaining its independence throughout the study ensuring transparent and objective oversight.

### Trial monitoring

The project will be monitored by the monitoring team of ICMR through regular site visits. The purpose of these visits would be to ensure strict adherence to the trial protocol, correct completion of the forms, and discuss any problems being faced by the research staff at the participating site.

### Data collection and monitoring

All history, examination, and investigations with assessment of drug compliance will be carried out at each follow-up and recorded in the CRFs. Adverse events will be noted throughout the study period. Lab investigations and ultrasound will be carried out as prehospital protocol.

#### Risk-based management

The quality-assured investigational product (IP)will be used for the trial and labeling of IP will be properly done mentioning the manufacturing and expiring date. The IP also will be stored in a clean and safe place.Interim analysis will be carried out after the completion of treatment of 90 enrolled participants (45 in each group) and the result will be reported to DSMB and IEC. The investigators will check each and every data collected in CRFs on a daily basis to check the missing data mainly related to primary outcome measures.The written consent form will be signed by each participant before their enrolment and it will be kept in safe custody and personal identification will be kept confidential.The project personnel will be trained about the study protocol and data collection before the initiation of the trial.

#### Confidentiality

The subjects will be informed by the investigator that all trial results recorded will be treated in strict confidence. During documentation and analysis of the trial, the individual subject will only be identified by their subject number, whereas the name of the subject and any personal data will come under data protection regulations.

#### Source documents

Source data is all information, original records of clinical findings, observations, or other activities in a clinical trial necessary for the reconstruction and evaluation of the trial. Source data are contained in source documents, i.e., hospital records, clinical and office charts, laboratory notes, memoranda, subjects’ diaries or evaluation check lists, pharmacy dispensing records, recorded data from automated instruments, copies or transcriptions certified after verification as being accurate and complete, subject files and records kept at the pharmacy, at the laboratories and at medico-technical departments involved in the clinical trial.

All information regarding clinical trial will be properly documented, carefully handled, and meticulously stored in order to ensure its accurate interpretation and verification.

#### Case report forms(CRF)

The study case report form is the primary data collection instrument for the study. All the data requested on the CRF will be recorded. All missing data will be explained. If a space on the CRF is left blank because the procedure was not done or the question was not asked, will write “N/D”. If the item is not applicable to the individual case, will write “N/A”. All entries will be printed legibly in black ink. If any entry error has been made, to correct such an error, will draw a single straight line through the incorrect entry and enter the correct data above it. All such changes will be initiated and dated. *Will not erase or white out errors.* For clarification of illegible or uncertain entries, will print the clarification above the item, then initial and date it.

#### Recordkeeping

The original records of subjects will be maintained at the trial site.

#### Study management at site

Trial site will be responsible for setting up an information system to keep track of all subjects screened, enrolled and will maintain a filing system to keep all study records, study protocol, related documentation, and medicine distribution records. The investigator will be responsible for the completeness and accuracy of the study materials.

#### Handling missing data

Strategies for handling missing dataData collection: to minimize missing data, we will implement thorough data collection procedures and follow up regularly with participants. Data checks and reminders will be employed to reduce missing data incidents.Imputation methods:▪ Multiple imputation: missing data will be addressed using multiple imputation techniques. This involves generating several imputed datasets to account for missing values, analyzing each dataset separately, and then combining the results to reflect the uncertainty due to missing data. This method assumes data are missing at random (MAR).▪ Last observation carried forward (LOCF): for missing data due to non-response at specific time points, LOCF may be used as a supplementary approach, assuming the last observed value is valid in the absence of further data.Model-based approaches:▪ Mixed-effects models: mixed-effects models will be used to handle missing data by accounting for both fixed and random effects, providing robust estimates despite incomplete data.▪ Maximum likelihood estimation (MLE): MLE will be employed to estimate model parameters, incorporating missing data directly into the estimation process under the assumption of data being missing at random.Sensitivity analysis: sensitivity analyses will evaluate the impact of different missing data handling methods on study results, assessing the robustness of findings under various assumptions about the missing data.Analysis of non-adherence to interventionaAnalysis of participants who do not adhere:Intention-to-treat analysis: participants will be analyzed according to their randomization assignment regardless of adherence. This approach maintains the benefit of randomization and provides an unbiased estimate of treatment effects.Per-protocol analysis: a per-protocol analysis will be performed for participants who adhere to the intervention as prescribed, assessing the effectiveness under optimal conditions.Compliance analysis:▪ Adherence rates: descriptive statistics will be used to calculate and characterize adherence rates.▪ Effectiveness among adherers: subgroup analyses will evaluate the effectiveness of the intervention among participants who follow the prescribed treatment.Instrumental variable analysis: if applicable, instrumental variable analysis may be used to address non-adherence issues by using variables correlated with adherence but not directly with the outcome.Imputation clarificationaImputation procedures:Multiple imputation approach:▪ Creating multiple imputed datasets: several datasets with imputed values will be created based on observed data and assumptions about missing data mechanisms.▪ Analysis of each dataset: each imputed dataset will be analyzed separately using the chosen statistical models.▪ Combining results: results from each imputed dataset will be combined using Rubin’s rules, accounting for within-imputation and between-imputation variability.Assumptions and validation: the assumptions behind the imputation methods will be validated, and sensitivity analyses will test the robustness of results under different imputation scenarios.Reporting: the imputation methods and rationale will be clearly reported, including the extent of missing data and the impact of imputation on the findings.

#### Non-enrollment of high-risk patients

Reasons for the non-enrollment of high-risk patients will be documented.

#### To address missing data from enrolled participants

Missing data will be managed using statistical techniques and enhanced data collection methods.

#### Loss of follow-up

Reasons for loss of follow-up will be recorded during the trial to assess impact.

#### Timelines with deliverables

Total study period: 36 months

Trial preparation: 01–03 months (drug supply, IEC approval, staff recruitment, etc.)

Recruitment: 03–33 months (treatment period: 21–25 weeks)

Statistical analysis and preparation of report: 03 months

Outcome analysis will be done after decoding the allocation sequence.

### Statistical analysis

Data will be coded and recorded in MS Excel spreadsheet program. SPSS v23 (IBM Corp.) will be used for data analysis. Descriptive statistics will be expressed in the form of mean/standard deviation and median/IQR for continuous variables, and frequency and percentage for categorical variable. Data will be presented in a graphical form wherever appropriate for data visualization using histograms/box-and-whisker plots/column chart for continuous data and bar chart/pie chart for categorical data. Group comparison for continuously distributed data will be done using independent sample “*t*” test when comparing two groups, and one-way ANOVA when comparing more than two groups. Post hoc pairwise analysis will be performed using Tukey’s HSD test in the case of one-way ANOVA to control for alpha inflation. If data will be found to be non-normally distributed, appropriate non-parametric tests in the form of Wilcoxon test/Kruskal–Wallis test will be used for these comparisons. Chi-squared test will be performed for group comparisons for categorical data. In case the expected frequency in the contingency tables will be found to be < 5 for > 25% of the cells, Fisher’s exact test will be applied instead. Linear correlation between two continuous variables will be explored using Pearson’s correlation (if the data will be normally distributed) and Spearman’s correlation (for non-normally distributed data) and *p* < 0.05 will be considered as statistical significant.

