The various clinical risk factors for PE are teenage pregnancy, primigravida, multiple gestation, history of diabetes, pre-existing hypertension, obesity, and previous history of HDP [13, 14]. NICE recommends screening for PE based on maternal characteristics along with medical, obstetric, and family history, which has a detection of 40% and 33% for preterm and term pre-eclampsia, respectively at a screen-positive rate of 11%. First-trimester quad was done at 11–13 + 6 weeks using maternal characteristics along with MAP, PIGF, and PAPP-A with/without UTPI and has a detection rate of 76% and 38% for preterm and term pre-eclampsia, respectively, at a FPR of 10% [11].

Preterm pre-eclampsia is due to defective placentation and low-dose aspirin (LDA) when started between 12 and 16 weeks of pregnancy corrects the imbalances in the levels of thromboxane A2 and prostacyclin, maintaining adequate uteroplacental blood supply. So aspirin improves defective placentation without increasing the risks of adverse maternal and perinatal outcomes [15].

Early prediction and prevention of pre-eclampsia would greatly contribute to improved maternal and perinatal health. Prevention of iatrogenic prematurity due to preterm PE is a very cost-effective measure. Aspirin is an inexpensive and widely available drug that has the potential to safely prevent preterm PE, resulting in reduced maternal and fetal morbidity and mortality [16]. Low-dose aspirin prophylaxis to prevent preterm pre-eclampsia is now recommended till 37 weeks of pregnancy in high-risk women [13].

Although low-dose aspirin has a good maternal and fetal safety profile, some authors have reported a higher incidence of intrapartum bleeding (2.9% aspirin users vs 1.5% nonusers), postpartum hemorrhage (10.2% vs 7.8%), postpartum hematoma (0.4% vs 0.1%), and neonatal intracranial hemorrhage (0.07% vs 0.01%) in aspirin users. A higher incidence of bleeding among aspirin users was present for those who had a vaginal birth but not those who had a cesarean delivery [15].

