While numerous randomized trials have investigated the prophylactic use of aspirin in the prevention of pre-eclampsia, the optimal dose still remains unclear. Prediction of preterm PE in the first trimester enables the caregiver in preventing this deadly disease using aspirin. All “at risk” women should be started with low-dose aspirin and earlier studies have used 75–81–100–150 mg [17–19]. The safety of 150 mg of aspirin needs to be validated and the minimum most effective dose for the prevention of preterm PE should be used. Hence, there is an urgent need for more evidence-based studies to resolve this dilemma about the appropriate dose of aspirin prophylaxis, weighing the benefit versus harm of aspirin.

Hence, this prospective randomized double-blind clinical trial is being carried out to compare 75 mg versus 150 mg Aspirin for the prevention of preterm pre-eclampsia in high-risk, screen-positive women.

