### Research question and justification

The primary objective of this study is to evaluate the efficacy and safety of two different dosages of low-dose aspirin (LDA), 75 mg and 150 mg daily, in preventing preterm pre-eclampsia in high-risk pregnant women. While LDA has been widely used and studied, the optimal dosage remains uncertain. Previous research indicates that aspirin can lower the incidence of preterm pre-eclampsia and its complications, but there is variability in the effectiveness of different dosages and timing of initiation.

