#### Secondary objectives

To evaluate feto-maternal outcomes in high-risk women receiving 75 mg versus 150 mg aspirin for the prevention of preterm preeclampsia.To compare the side effects of 75 mg versus 150 mg aspirin during pregnancy.

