### Sample size

The sample size calculation is based on a study by Kumar (2020), according to which the expected proportion of PE in the two groups receiving 75 mg versus 150 mg aspirin was 17% and 6.5% respectively [10].

The sample size has been calculated according to the formula given by Sahai and Kurshid (1996):^74^
$$\text{Sample size}\;N=\frac{\left\{z_{\left(1-\alpha/2\right)}\sqrt{2 \ast \overline p\left(1-\overline p\right)}+z_{\left(1-\beta\right)}\sqrt{p_1\left(1-p_1\right)+p_2\left(1-p_2\right)}\right\}^2}{\left({\text{p}}_1-{\text{p}}_2\right)^2}\;where\;\widehat p=\frac{p_1+p_2}2$$

Expected proportion in the first group: *p*₁ = 0.17 (17%).

Expected proportion in the second group: *p*₂ = 0.065 (6.5%).

*p̂*: (*p*₁ + *p*₂)/2 = 0.1175.

Type I error: *α* = 0.05 (5%), $${z}_{\left(1-\alpha /2\right)}$$ = 1.96, CI = 95%

Type II error: *β* = 0.20 (10%), $${z}_{\left(1-\beta \right)}$$ = 0.842, power = 80%

Based on the formula and values given above, the sample size calculated per group is 146.6 ≈ 147 (total 294).

Allowing for 20% attrition, we get a sample size of 294/0.8 ≈370 (185/group).

Thus, with 80% power and 95% confidence interval, the minimum sample size required for the study is *185* in each group (total 370).

Reference for the formula:

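### The only between-arm analysis stated for binary safety outcomes is a significance test with little power for bleeding; report risk differences with confidence intervals and do not read non-significance as safety

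*Protocol article*

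**What the plan says.** Safety is part of the stated purpose in several places. The Introduction says "The safety of 150 mg of aspirin needs to be validated". The section Research question and justification opens with "The primary objective of this study is to evaluate the efficacy and safety of two different dosages of low-dose aspirin (LDA", and the abstract's Methods paragraph likewise pairs efficacy with safety. The formal list under Secondary objectives includes "To compare the side effects of 75 mg versus 150 mg aspirin during pregnancy". The formal primary objective and the hypothesis concern prevention of preterm pre-eclampsia only.

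The Secondary outcomes section lists GI bleed, abruption, postpartum hemorrhage, hematoma and neonatal intracranial bleeding, among others.

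For categorical outcomes, Statistical analysis gives frequencies and percentages and then the test: "Chi-squared test will be performed for group comparisons for categorical data". Fisher's exact test replaces it when more than 25% of cells have an expected count below 5, and p < 0.05 counts as significant. No effect estimate or interval is named for any between-arm comparison.

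Sample size rests on pre-eclampsia at 17% versus 6.5%. It gives 147 per group, or 185 per group after a 20% allowance for attrition.

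For bleeding, the Introduction cites a comparison of aspirin users with non-users: intrapartum bleeding 2.9% versus 1.5%, and "postpartum hemorrhage (10.2% vs 7.8%), postpartum hematoma (0.4% vs 0.1%), and neonatal intracranial hemorrhage (0.07% vs 0.01%) in aspirin users".

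**The concern.** A test of no difference can detect harm or fail to detect it. It cannot show that a dose is acceptably safe. That weakness is mild when power is high and serious when power is low, because a non-significant result is then expected whether or not the harm is there.

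Here the sample was set for a 10.5-point difference in pre-eclampsia, while the bleeding excesses cited in the Introduction run from 0.06 to 2.4 points. A trial meant to weigh benefit against harm between two doses, and to inform guidelines, would most likely end with a row of non-significant bleeding comparisons. Without an estimate and an interval beside them, a reader cannot see how large an excess the data still allow.

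**Working it through.** **1. The plan's own sample size.** With p1 = 0.17, p2 = 0.065 and mean 0.1175, the formula in Sample size gives

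(1.96·√(2·0.1175·0.8825) + 0.842·√(0.17·0.83 + 0.065·0.935))² / 0.105² = (0.8926 + 0.3783)² / 0.011025 = 146.5.

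The protocol prints 146.6 and rounds to 147. Then 294/0.8 = 367.5, which the protocol rounds to 370. The size reproduces, and it concerns pre-eclampsia only.

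**2. Power for bleeding under the stated rule.** Inputs are n = 185 per arm (all randomised) or 147 (after 20% attrition), two-sided 0.05, and the rates cited in the Introduction. The documents give no rates by dose. I therefore assume that 75 mg has the non-user rate and 150 mg the user rate. The cited intrapartum rate is a stand-in, because the outcome list specifies that item as GI bleed.

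Let a and b be the event counts on 150 mg and 75 mg. Then

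Power = Σ Σ Bin(a; n, p150) · Bin(b; n, p75) · 1[p-value < 0.05 and a > b].

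With equal arms, the expected event count in each arm is (a + b)/2. If that is below 5, two of four cells (50%) fall short and Fisher's test applies. Otherwise the uncorrected chi-squared test applies. The miss rate is 1 − power.

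| Outcome, 75 mg to 150 mg | Power at 185 / 147 | Missed at 185 / 147 |
|---|---|---|
| Postpartum hemorrhage 7.8% to 10.2% | 12.3% / 10.4% | 88% / 90% |
| Intrapartum bleeding 1.5% to 2.9% | 9.0% / 5.4% | 91% / 95% |
| Hematoma 0.1% to 0.4% | below 0.01% | essentially 100% |
| Neonatal intracranial hemorrhage 0.01% to 0.07% | about 0% | essentially 100% |

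**3. Larger harms**, since the assumed excess may be wrong:

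| Outcome, 75 mg to 150 mg | Power at 185 / 147 | Missed at 185 / 147 |
|---|---|---|
| Postpartum hemorrhage 7.8% to 15.6% | 65.8% / 55.7% | 34% / 44% |
| Postpartum hemorrhage 10.2% to 15.3% | 31.7% / 26.0% | 68% / 74% |
| Intrapartum bleeding 2.9% to 5.8% | 27.2% / 21.2% | 73% / 79% |

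By the normal approximation, 80% power for postpartum hemorrhage needs about 17.4% (185 per arm) or 18.9% (147 per arm) against 7.8%. Against 10.2% it needs about 20.7% or 22.2%. Put the other way, 80% power for 7.8% versus 10.2% needs

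(1.96·√(2·0.09·0.91) + 0.842·√(0.102·0.898 + 0.078·0.922))² / 0.024² ≈ 1.285 / 0.000576, or about 2,230 per arm.

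**4. What an interval would show.** Suppose both arms have the same observed postpartum hemorrhage rate, near 10%. At 19/185 (10.27%) the Wilson limits are 6.67% and 15.48%. The Newcombe half-width is √((10.27 − 6.67)² + (15.48 − 10.27)²) = 6.3 points. At 15/147 it is 7.1 points.

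At the cited rates, a simple 95% interval for the difference of +2.4 points runs from −3.4 to +8.2 at 185 per arm and from −4.1 to +8.9 at 147.

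**The case against.** The strongest reply is that the document contains no error. Statistical analysis is a generic paragraph that matches tests to data types and sets no safety decision rule. A reader might infer that safety is decided by these tests alone, or that p > 0.05 will be accepted as proof that 150 mg is safe. The documents support neither reading. No passage equates non-significance with safety. Adverse events are also classified by type, severity and relationship to treatment (Safety recording), and the DMC and the DSMB both review safety data. This part of the objection stands. Those provisions serve description and monitoring, though, and none states another between-arm comparison for the final report.

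Second, the word validated appears in the Introduction as a gap in the field, and low power for rare secondary harms is normal in a trial sized on its primary outcome. Both are fair. But Research question and justification puts safety into the primary objective as worded there, so safety is more than background.

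Third, the cited excesses compare users with non-users, while both arms here take aspirin. That also stands: the 88–100% range is conditional and is not a prediction for these two doses. A smaller dose excess would lower power further, and step 3 shows that larger ones are still often missed.

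Fourth, effect estimates may be in an analysis plan that is not shown. For that reason the missing interval would be a weak point taken alone. What carries the point is what the document does state: a safety aim, a significance-only comparison, and a sample sized on another outcome.

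A single pooled bleeding endpoint might seem a natural remedy. I do not propose it. The Introduction links abruption to pre-eclampsia itself, so pooling abruption with other bleeding could hide a harm.

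**Conclusion.** The point holds in a limited form. The one between-arm analysis stated for binary safety outcomes says little about harm at this sample size. Power is about 0–12% for excesses of the size cited in the Introduction, if those carry over from users versus non-users to 150 mg versus 75 mg. For a doubling of postpartum hemorrhage from 7.8% it is 56–66%. A non-significant bleeding comparison could therefore be misread as reassurance, and the plan should guard against that. The weakness lies in how the safety comparison is framed and reported; the primary efficacy analysis and its sample size are not affected.

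**What to change.** In Statistical analysis, state that each bleeding and side-effect outcome is reported as a risk difference (150 mg minus 75 mg) with a 95% confidence interval, for example Newcombe's. State also that the safety conclusion is worded from the interval, including the largest excess it does not exclude, and that p > 0.05 is not evidence of equal safety. The tests may stay alongside.

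In the Introduction and in Research question and justification, say that the trial estimates the comparative safety of the two doses rather than validates it. In Sample size, note that the number is set for pre-eclampsia only, and give the expected precision for postpartum hemorrhage: a half-width of about 6 to 7 points at a rate near 10%.

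The cost is a few sentences, with no new data, visits or participants. The downside is a more modest safety claim.

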Prediction model for PE < 37 weeks using maternal factors + MAP along with PAPP-A and PIGF has a detection rate (DR) of 73% with 10% FPR. Adding uterine artery PI (UTPI) increases DR to 80% with FPR of 10%. 1 T Quad will be done using Perkin Elmer LifeCycle 7.0 software on Victor 2D Instrument (Time Resolved Fluorescence—DELFIA). PerkinElmer LifeCycle 7.0 software will generate a report in which a woman’s individual risk for developing preterm pre-eclampsia will be clearly presented and color coded (red = increased risk). The day IT Quad will be carried out will be visit 0.

Women with risk for preterm PE 1:100 and greater will be labeled as screen positive or high risk. Prior to any trial-related activity, the investigator will be given the verbal information and written information in a printed form about the trial to the participant/guardian(s) which they can read and understand. The investigator would ensure that the participant is fully informed about the aims, procedures, discomforts, and expected benefits of the trial. It will be emphasized that participation is voluntary and participants have the right to opt out of the trial at any time without any prejudice. A voluntary, signed informed consent will be obtained from the participant prior to clinical trial-related procedure.

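### The stated primary test is valid but unadjusted: using the 1T Quad risk already held for every randomised woman could add power at almost no cost, and the planned pooling still needs a named estimate

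*Protocol article*

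**What the plan says.** **Outcome.** Under Primary outcomes, the article counts the women in each arm who develop preterm pre-eclampsia, so each woman contributes one yes/no result.

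**Test.** The Statistical analysis section labels no test as primary. Its rule for such data is: "Chi-squared test will be performed for group comparisons for categorical data". If expected counts are "found to be < 5 for > 25% of the cells, Fisher’s exact test will be applied instead". It names no risk difference, risk ratio, odds ratio, confidence interval or covariate.

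**Missing data.** Handling missing data plans multiple imputation, in which "each imputed dataset will be analyzed separately using the chosen statistical models", and then "results from each imputed dataset will be combined using Rubin’s rules, accounting for within-imputation and between-imputation variability". It does not say which model serves preterm pre-eclampsia. It adds that "mixed-effects models will be used to handle missing data by accounting for both fixed and random effects", and mentions maximum likelihood, but ties neither to this outcome.

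**Baseline risk.** The section on the first-trimester quadruple test says the software produces a report in which "a woman’s individual risk for developing preterm pre-eclampsia will be clearly presented and color coded". The Inclusion criteria admit only women who screen positive on this test, and the cut-off is a risk of 1:100 or greater. Every randomised woman therefore has a score. No stated analysis uses it beyond eligibility.

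**The concern.** Two things are left on the table.

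First, a baseline score built to predict this very endpoint is held for everyone and not used in the comparison. If it still separates higher-risk from lower-risk women among those enrolled, adjusting for it buys power without recruiting anyone.

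Second, Rubin's rules combine an estimate and its variance across imputed datasets. A chi-squared or Fisher test delivers a p-value. The article therefore sets out a pooling step without naming what goes into it, and with 20% attrition allowed for, that step could bear on the main result. A p-value alone also does not help with the benefit-against-harm weighing that the Introduction gives as the reason for the trial; a risk difference with a confidence interval does.

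**Working it through.** **1. The plan's own figure.** From Sample size: p₁ = 0.17, p₂ = 0.065, mean 0.1175, z = 1.96 and 0.842.

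- 1.96 × √(2 × 0.1175 × 0.8825) = 0.8926
- 0.842 × √(0.17 × 0.83 + 0.065 × 0.935) = 0.3783
- n = (0.8926 + 0.3783)² / 0.105² = 1.6152 / 0.011025 = 146.5, so 147 per arm (the article prints 146.6, then 147)
- 294 / 0.8 = 367.5, stated as 370

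The figure reproduces. By the same normal approximation, power is 80.1% at 147 per arm and 88.3% at 185 per arm. The trial was sized for an unadjusted comparison, and the unadjusted test matches that.

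**2. What adjustment would add.** Trials were simulated at 17% versus 6.5%, 147 per arm, with a logistic model containing arm and a normally distributed baseline score. Intercepts were solved so that the marginal rates stayed at the planning values. There were 4,000 runs per setting, so the simulation standard error is about √(0.82 × 0.18 / 4000) = 0.6 points. The AUC is the score's discrimination among enrolled women and is an assumption.

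| Assumed AUC | Chi-squared | Adjusted, Wald | Adjusted, likelihood ratio |
|---|---|---|---|
| 0.50 | 0.819 | 0.808 | 0.823 |
| 0.64 | 0.822 | 0.818 | 0.829 |
| 0.75 | 0.815 | 0.847 | 0.857 |
| 0.82 | 0.814 | 0.876 | 0.884 |

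Under the null (2,000 runs each), rejection was 4.5–5.6% for chi-squared, 4.7–5.3% for the adjusted Wald test and 5.3–6.2% for the likelihood ratio test.

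Enrolment only at 1:100 or greater cuts the score off on one side. Further simulations that included one-sided, skewed scores gave about 82% unadjusted. Adjusted power was 82% at AUC 0.64, 83% at 0.68, 84–87% at 0.75 and 89–91% at 0.81–0.82. Null rejection was 5.2% (chi-squared) and 4.6% (adjusted).

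**3. Whether the pooling can be done.** Setup: 185 per arm, 20% of outcomes missing at random, 20 imputations, 1,500 runs.

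| Quantity pooled | Power | Type I error |
|---|---|---|
| Risk difference, Rubin's rules | 82.1% | 4.5% |
| Log odds ratio, Rubin's rules | 80.3% | 3.8% |
| Chi-squared statistic, D2 rule | 81.7% | 4.4% |

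All three work. Only Fisher p-values have no direct Rubin pooling.

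**4. How often Fisher would apply.** A 2×2 table has four cells, so more than 25% means at least two. With equal arms, each event cell has an expected count of half the total events, so Fisher applies when total events are below 10. At the planning rates, expected events are 147 × (0.17 + 0.065) = 34.5, and the chance of fewer than 10 is about 6 in 100 million. At the 4.3% and 1.6% that the article quotes from a trial of placebo against 150 mg, the chance is 63% at 147 per arm and 35% at 185. Those rates are only illustrative, since a placebo rate is not a 75 mg rate.

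**The case against.** The strongest case against is that nothing here is wrong. The unadjusted test keeps its type I error and fits the sample size formula. No stratification is described that would call for adjustment. Chance imbalance in baseline risk is ordinary sampling variation that the standard error already covers. Covariates and effect measures are commonly left to a statistical analysis plan, which is not shown. All of that stands, and it is why this is offered as an improvement.

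The size of the gain is also open. The detection rates the article quotes describe the screening model, not women already above the cut-off. Uterine artery Doppler is optional, so scores may rest on different marker sets. With an AUC of 0.64 or less there is no gain.

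A reader might infer three stronger claims that the documents do not support:

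- **That the test cannot be combined with Rubin's rules.** It can be pooled by the D2 rule, or through the risk difference or log odds ratio from the same table. The article also does not say that chi-squared is the analysis run in each imputed dataset.
- **That the trial is already short of power.** At its own planning rates it has 80.1% with 147 per arm.
- **That the 1T Quad risk is the strongest baseline predictor among these women.** No figure in the article shows this.

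What remains is that the one comparison rule stated for this outcome leaves an available covariate unused, and that the pooling step has no named input.

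**Conclusion.** The point holds as a cheap improvement, not as an error. The stated comparison is valid. Pre-specified adjustment for 1T Quad risk would add between nothing and roughly 9 power points at 17% versus 6.5% and 147 per arm: about 82% unadjusted, against about 82% (AUC 0.64 or less), 84–87% (AUC 0.75) or 88–91% (AUC about 0.82). Type I error stays near 5%. These figures rest on assumed AUCs, on the protocol's event rates and on a logistic model that is linear in the score.

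The link between the test and the imputation plan is unspecified rather than contradictory, and naming an estimate closes it, with or without the covariate. The Fisher branch, which has no direct Rubin pooling, matters only if events are far fewer than planned.

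**What to change.** Before the allocation is decoded, pre-specify the following:

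- **Primary analysis:** intention-to-treat logistic regression of preterm pre-eclampsia on arm and log 1T Quad risk.
- **Reporting:** standardised (marginal) risk difference and risk ratio, each with a 95% CI.
- **Pooling:** Rubin's rules across imputations, on the log-odds or risk-difference scale, with the scale named.
- **Supporting analysis:** the unadjusted chi-squared or Fisher test on observed data.
- **Fallback:** an exact rule, fixed in advance, for when the unadjusted test replaces the model, such as a minimum total event count or non-convergence. Without such a rule, the choice of primary analysis would depend on the data.

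The cost is wording and slightly more analysis work. The covariate is already collected. The one technical downside is that the model gives a conditional odds ratio, which has to be standardised to the risk scale before it is reported.
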